### Outcomes

Primary Outcomes: Assess sensitivity, specificity, positive and negative predictive value, positive and negative agreement, accuracy, and receiver operating curves (at various CT value cutoffs), to determine the efficacy the new rectal swab approach.

Secondary outcomes: Acceptability of the rectal swabs in comparison to the gold standard of bulk faeces testing. This will be measured by asking participants which sampling method they preferred, and collecting information from participants in relation to any adverse events that may have occurred.

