## Abstract

Obtaining a stool specimen for diagnostic testing of enteric conditions (e.g., gastroenteritis) can be a challenging and unpleasant experience. A person is required to obtain a sample pot from a healthcare location, return home and wait until they have a bowel motion, and then deal with the challenges of returning the sample to the clinic or pathology centre. This trial aims to identify whether the simpler approach of obtaining a rectal swab is effective for diagnosing enteric conditions. Recruitment will take place in a variety of settings, including suspected norovirus clusters, Hepatitis A clusters, in both hospital, and community settings. We will compare paired stool and rectal swab sample polymerase chain reaction (PCR) testing to determine whether rectal swabs are a reliable proxy for faecal sampling. Persons who would normally be provided with a faecal specimen container, will also be provided with a rectal swab for self-collection or clinician-collection (within 24 hours of the bulk faeces collection). We will assess the sensitivity, specificity, positive predictive value, negative predictive value using standard confusion matrix. The gold standard reference will be considered the bulk faeces PCR tests. We hypothesise that rectal swab PCR testing will be equally as effective as bulk faeces PCR testing. If successful, rectal swab PCR testing could be implemented as routine practice with several key benefits. Firstly, it would improve the patient experience by conveniently enabling stool collection at the point of care, which is rarely possible currently. Secondly, it would reduce healthcare costs, and streamline collection processes by eliminating the need for persons to return to a clinic to deliver specimen. Thirdly, the ease of testing will likely increase testing rates and compliance, leading to better diagnoses and more accurate clinical care. The protocol described has the potential to revolutionise daily clinical practice.

**Trial registration**: Australian New Zealand Clinical Trials Registry (ANZCTR): ACTRN12624000095561.

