#### Primary outcomes.

We will assess the sensitivity, specificity, positive and negative predictive value, and positive and negative agreement value, using 2x2 tables. The gold standard will be bulk faeces PCR testing. Sensitivity is the proportion of individuals with the disease who test positive with rectal swabs. We will assess the cycle threshold (CT) values using general linear models if the relationship is linear as expected and estimate the receiver operating curves and areas under the curve to assess for the potential to need differential CT value cutoffs. All results will be reported using 95% confidence intervals.

The R statistical suite will be used for all analyses and data visualisation. All estimates will be presented with 95% confidence intervals (CI). P-values <0.05 are deemed significant, and p-values <0.1 are considered trends.

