#### Interim analysis.

Interim analyses will be part of a yearly steering committee meeting or at every 100 participants recruited, whichever comes first. The trial will implement a modified alpha spending function to guide decisions on early stopping. Initially, at 100 participants, a non-inferiority margin of 0.35 will be applied. This threshold will decrease by 0.05 at each subsequent interim analysis, reaching a final margin of 0.10 after 500 participants have been recruited. If the observed difference exceeds the non-inferiority margin at an interim analysis, the trial will be stopped for inferiority.

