#### Objectives of interim analysis.

Recruitment Rates: Assess the rate of recruitment and discuss the barriers and facilitators to successful participant recruitment.Safety Monitoring: Ensure participant safety by identifying any significant adverse events early. Review adverse event reports, including severity, relatedness, and unexpected events. Analyse differences in safety profiles between the rectal swab and bulk faeces groups.Efficacy Assessment: Non-inferiority assessments will be performed to monitor for inferiority of rectal swab PCR in comparison with traditional bulk faeces testing. Evaluate the primary endpoint of difference of accuracy of specimen collection methods, the rate of pathogen detection.Trial Continuation Decision: Provide data to support decisions on continuing, modifying, or stopping the trial.Compliance and Protocol Adherence: Assess the adherence to study protocols, including the proper collection and handling of specimens.

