#### Decision rules.

Stopping for Safety: Predefined criteria for stopping the trial if a significant safety concern are identified; for instance, if the incidence of severe adverse events is above what is expected.Stopping for Efficacy: Criteria for stopping the trial early if rectal swabs show clear and overwhelming evidence of inferiority, based on predefined statistical thresholds and thus it is futile to continue. A cutoff of 0.35 difference in accuracy for inferiority with an alpha of 0.05 at interim analyses will be used to support decisions on continuing, modifying, or stopping the trial. As this is a diagnostic test trial, the decision to stop the trial must be multifactorial in nature and made by the Trial Steering Committee.

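### Several accuracy measures are called primary with none leading, and the sizing, the interim endpoint and the margins rest on different ones, so one data set can give opposite answers

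*Protocol article*

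**What the plan says.** The protocol article describes what decides the trial in six places.

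- **Abstract:** "We hypothesise that rectal swab PCR testing will be equally as effective as bulk faeces PCR testing". No measure or margin is attached.
- **Outcomes:** the primary outcomes are to "Assess sensitivity, specificity, positive and negative predictive value, positive and negative agreement, accuracy, and receiver operating curves (at various CT value cutoffs"). They are not ranked.
- **Statistical methods, Primary outcomes:** "We will assess the sensitivity, specificity, positive and negative predictive value, and positive and negative agreement value, using 2x2 tables". Cycle-threshold models and ROC analysis follow. Overall accuracy is not in this list.
- **Objectives of interim analysis:** "Evaluate the primary endpoint of difference of accuracy of specimen collection methods, the rate of pathogen detection". This is a single endpoint described by two quantities.
- **Interim analysis:** "Initially, at 100 participants, a non-inferiority margin of 0.35 will be applied", later "reaching a final margin of 0.10 after 500 participants have been recruited". The measure is not named. The consequence is one-directional: "If the observed difference exceeds the non-inferiority margin at an interim analysis, the trial will be stopped for inferiority".
- **Decision rules:** "A cutoff of 0.35 difference in accuracy for inferiority with an alpha of 0.05 at interim analyses". Here the measure is accuracy.

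The Sample size calculation uses sensitivity only: 61 pairs at 30% positive, 92 at 20% positive, and 73 positives per pathogen subgroup.

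**The concern.** The trial intends to replace bulk faeces testing with swabs, so its readers need to know which number carries that conclusion. The text points to sensitivity (sizing), accuracy (stopping cutoff), detection rate (interim endpoint) and an unranked list (Outcomes).

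These are not interchangeable. Accuracy is dominated by negatives when most samples are negative, so it can stay high while many positives are missed. A difference in detection rate compares the two positive fractions, so positives that the swab misses and positives found only by the swab cancel. A swab that misses one positive in five could therefore be judged close to bulk faeces on two of these measures and clearly short on sensitivity.

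**Working it through.** **1. What the sizing rests on.** The precision formula is N = 1.96² × Se(1 − Se) / d² / prevalence, with Se = 0.95. The half-width d is not given in the text; the values below are those that reproduce the article's figures.

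- d = 0.10, 30% positive: 60.8, so 61.
- d = 0.10, 20% positive: 91.2, so 92.
- d = 0.05, positives only: 72.99, so 73.

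All three published figures are thus reproduced as 95% interval-width targets for sensitivity. None is power for a test on any measure.

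**2. How many measures are distinct.** With bulk faeces PCR as reference, positive and negative agreement in their usual form are sensitivity and specificity. The eight named items reduce to about six.

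**3. One table, several candidate measures.** The 25% positivity is the literature figure in the Sample size calculation, and 600 is the ceiling given there. Sensitivity 80% and specificity 98% are assumptions. This gives 150 reference positives (120 detected, 30 missed) and 450 reference negatives (441 negative on swab, 9 swab-only positives). Intervals are Wilson 95%, with a Wald interval for the paired difference.

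| Measure | Estimate | 95% CI | Against 0.10 |
|---|---|---|---|
| Sensitivity, 120/150 | 0.800 | 0.729 to 0.856 | shortfall 0.20; outside even at the upper limit |
| Specificity, 441/450 | 0.980 | 0.962 to 0.989 | inside |
| Accuracy, 561/600 | 0.935 | 0.912 to 0.952 | shortfall 0.065; inside, with its interval |
| Detection rate, 129/600 − 150/600 | −0.035 | −0.055 to −0.015 | inside, with its interval |

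An exact McNemar test on the same table gives p = 0.001, so the detection-rate comparison itself reads as within margin and as significantly worse.

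**4. How far accuracy can hide missed positives.** Accuracy = prevalence × Se + (1 − prevalence) × Sp. The reference has accuracy 1 by definition, so a 0.10 margin means accuracy of at least 0.90. At 25% positive and Sp = 0.98, Se = (0.90 − 0.75 × 0.98) / 0.25 = 0.66. Across 20–30% positive and specificity 95–100%, this break-even sensitivity runs from 50% to 78%.

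**5. Cancellation in the detection rate.** At 600 pairs and 25% positive, sensitivity 80% with specificity 93.3% gives 30 missed and 30 swab-only positives. The detection-rate difference is exactly 0 (−0.025 to 0.025).

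**6. What a formal goal would cost.** Suppose the goal were a Wilson 95% lower bound above 0.90 for sensitivity, with true sensitivity 95%.

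- 150 positives (600 pairs, 25% positive): at least 143 detections are needed, since 142 gives a lower bound of 0.898. The probability is 52%.
- 312 pairs (three swabs a week for 104 weeks, the low end in Timeline), 20–30% positive, about 62 to 94 positives: 18% to 30%.
- 18 positives (92 pairs, 20% positive): 18 of 18 gives a lower bound of 0.824, so the goal cannot be met.
- 230 positives (920 pairs at 25% positive): about 82%.

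These probabilities are for sensitivity alone. Requiring specificity as well cannot raise them.

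**The case against.** Much of the other side stands.

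- Reporting sensitivity, specificity and predictive values together is normal in a paired accuracy study sized on interval width.
- The article commits to all the listed 2×2 measures with 95% confidence intervals, so a sensitivity of 80% would be published. A reader might infer that the plan allows an unfavourable measure to be left out; it does not.
- Sensitivity is the lead measure in practice: it is the only one sized, and the Primary outcomes section spells out its meaning.
- A reader might infer that the interim section substitutes a different endpoint. It does not quite do so: it names accuracy, which is on the Outcomes list, and then adds detection rate as if it were the same thing.
- A reader might also infer that the cycle-threshold cutoff behind the headline sensitivity is open. The documents do not support that. The varying cutoffs qualify the ROC curves, and Minimum data requirements records a positive/negative result for each sample.
- It would be wrong to say that a poor swab is bound to succeed on something. A high specificity that passes because it is truly high is a correct result.
- A full decision rule and the multiplicity method may sit in a statistical analysis plan that is not shown. Their absence is not the point here.

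What remains is what the article itself states: two primary lists that differ on accuracy, an interim endpoint that merges two different quantities, and a final margin with no measure that serves only to stop the trial. Surviving that rule does not show that the methods are equally effective.

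**Conclusion.** The concern holds as an inconsistency in the primary measure and should be fixed. The sections cannot all be followed as written, and the choice between them can change the answer. In the illustrated table, sensitivity falls 0.20 short while accuracy and detection rate both lie within 0.10. At 25% positive and 98% specificity, accuracy stays within 0.10 down to a sensitivity of 66%.

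The size rests on assumed sensitivity, specificity and 600 pairs. Sensitivity of 80% is below the article's expectation of more than 90%. Applying 0.10 to each measure is also an assumption, because the article does not say what that margin applies to. The inconsistency in the text does not depend on these figures.

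**What to change.** 1. In Outcomes and in Primary outcomes, name sensitivity and specificity as co-primary. Define them as positive and negative agreement with bulk faeces PCR, using the laboratory's routine positive/negative call. This fits the sensitivity-based sizing.
2. State that the conclusion on equal effectiveness rests on the 95% confidence intervals of this pair.
3. Label predictive values, overall accuracy, and the ROC and cycle-threshold analyses as secondary.
4. In Objectives of interim analysis, delete the detection-rate phrase and refer to the same pair.
5. In Interim analysis and Decision rules, state that the margins apply to that pair.
6. If a formal goal is added, for example both lower bounds above 0.90, disclose its power as worked out above. Otherwise report the co-primaries as estimates without a pass/fail claim.

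**Cost:** Items 1 to 5 are wording changes and need no extra data. A formal goal is not free: about 920 pairs at 25% positive would be needed for roughly 80% power on sensitivity, above the article's ceiling of 600. A favourable accuracy or detection-rate result could no longer carry the conclusion, and any equivalence claim would have to be stated less strongly.

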### Timeline

Participant recruitment is expected to commence in early 2025. Recruitment and data collection are expected to be completed within two years. Results are expected shortly after, placing the trial completion date in late 2027 or early 2028. It is expected that an average of 3–6 swabs will be obtained per week across collection sites. Some situations, such as outbreaks or mass gathering events, will allow for greater numbers of swabs to be collected in a small timeframe. After participants return the test samples, they will receive a follow-up phone call. Results of the bulk faeces test will be returned to the patient by the clinician that requested the test.

### Sample size calculation

A sample size analysis with a wide range of input parameters, as described by Hajian-Tilaki 2014, demonstrates that less than 600 samples will be sufficient to cover a range of diseases (Fig 2) [16]. Assuming that 30% of samples will contain an organism (“proportion positive”) with an expected sensitivity of at least 95% (“sensitivity priors”) means we will require a sample size of no more than 61 paired samples. As the prevalence of disease in samples decreases, the sample size required is higher. For a sensitivity of 95% and a prevalence of 20%, the sample size increases from 61 to 92. These estimates are based on general sensitivity assumptions and a simplified disease prevalence model, with the literature reporting non-specific prevalence to be approximately 25%, and sensitivity estimates typically >90% [17–20]. These estimates may change slightly as recruitment progresses and the distribution of pathogens becomes clearer. To address potential variability across different pathogens, stratified analyses will be conducted. Power calculations for key pathogen subgroups indicate that, for a sensitivity of 95% (with a range of 90–99%), a minimum of 73 positive samples is required per pathogen subgroup.

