Studies have long compared rectal swabs vs bulk faeces testing. The results are varied, depending on the year the study was performed. An early study examining 700 specimens tested with MacConkey’s medium in 1940 during a Sonne dysentery outbreak (*Shigella sonnei* sp. outbreak) found that rectal swabbing was far superior to bulk faeces culture to detect an organism [8]. Rectal swabbing became the standard for a period of time This was disputed later in 1954 after a group examined 3,183 index cases looking for a variety of organisms to which they concluded that the *“…626 [bulk faeces] specimens all showed abnormalities which could be demonstrated only by microscopy or simple chemical methods, for which the rectal swab is quite unsuitable”* [9]. Since then, huge changes have occurred to our detection methods (e.g., culture media) and the advent of PCR testing for multiple organisms at once.

More recent studies demonstrate that the differences between rectal swabs and faecal samples is driven by the type of test (bacterial microscopy and culture vs viral PCR). A phase I clinical study for a live oral attenuated *Salmonella* Typhi vaccine strain found that when compared with faecal culture, rectal swabs were 64% sensitive and 90% specific [10]. A recent study on paired samples found that for bacteria, the sensitivity was 86.5% (95% CI 79.5%, 91.8%) when PCR was performed and 61.4% (95% CI 52.4%, 69.9%) when culture for bacteria was performed, indicating better performance for PCR [11].

It has been shown in small studies that rectal swabs are likely accurate. Studies have now shown that during testing for various enteric organisms (viruses and bacteria) in Rwandan children there was no significant difference in detection rate between faeces and rectal swabs for any agent, reflecting that pathogen concentration was far above the limit of detection in the majority of cases [12]. A similar paired sample study focusing on norovirus found a sensitivity of rectal swabs that was greater than 97%, and in one case detected norovirus in the swab, but not in the bulk faeces [13].

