The outcome of this project will transform clinical practice for doctors and patients. It will make testing far more convenient and allow for point-of-care testing to become a reality for enteric organisms. Currently, many people leave the emergency department without a faecal test because they could not produce a specimen while they were with the clinician. Rectal swabbing would make the diagnosis, and better care available for these patients. Public Health practitioners would be able to perform mass testing after small or large scale outbreaks, such as those caused by hepatitis A, norovirus or other organisms found in faeces [14,15]. Doctor’s in the emergency department would be able to obtain swabs on demand for testing that would expedite time spent in ED and, with the earlier diagnosis, length of stay in hospital. Most importantly, for patients, it means that they no longer must go home, wait until they need to have a bowel motion, and then return to the hospital or GP clinic with their sample, as it can be done on demand, on-site (in a private situation). Thus, rectal swabbing can transform clinical practice through earlier diagnosis, shorter length of stay’s and greatly improving the patient experience. This study aims to demonstrate that self-collected or clinician collected rectal swabs are a valid alternative method of testing when compared to bulk faeces testing for a wide range of enteric organisms such as bacterial, viral, and parasitic/protozoan. The intended outcome of this project is to replace bulk faeces testing with rectal swabbing in daily clinical and public health practice.

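### The minimum of 73 positives per pathogen subgroup holds only at about 95% sensitivity; at the protocol's own bacterial PCR figure of 86.5% it gives about ±8 points, not ±5

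*Protocol article*

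**What the plan says.** The Sample size calculation section first gives overall figures at a sensitivity of 95%: 61 pairs if 30% of samples are positive and 92 if 20% are. It puts prevalence in the literature at about 25% and sensitivity typically above 90%. It then turns to stratified analyses and states that "for a sensitivity of 95% (with a range of 90–99%), a minimum of 73 positive samples is required per pathogen subgroup". No half-width is given, and no other subgroup minimum is offered for a different sensitivity.

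The Introduction reports class-specific results from paired samples. In one study, "for bacteria, the sensitivity was 86.5% (95% CI 79.5%, 91.8%) when PCR was performed". Another paired study, on norovirus, found "a sensitivity of rectal swabs that was greater than 97" per cent. The stated aim covers "a wide range of enteric organisms such as bacterial, viral, and parasitic/protozoan", with the intention of replacing bulk faeces testing in practice. Statistical methods plans a subgroup analysis by disease type and names viral and bacterial as its examples. Under Primary outcomes, "All results will be reported using 95% confidence intervals".

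**The concern.** The positives needed for a given interval width depend on Se(1 − Se), which rises quickly as sensitivity falls from 95%. One minimum computed at 95% is therefore too small for any class expected to do worse. The protocol's own bacterial PCR estimate lies below 90%, and its confidence interval excludes 95%.

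What is at stake is how the bacterial subgroup result is read. A reader of the sample size section would take 73 bacterial positives as enough for the same precision as in the viral subgroup. If sensitivity is near the cited figure, the interval will be about one and a half times as wide, in the class where the protocol's own evidence puts the swab furthest from bulk faeces.

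**Working it through.** **Inputs.** Sensitivity 95%, range 90–99%, and 73 positives (Sample size calculation). Bacterial PCR sensitivity 86.5%, interval 79.5% to 91.8% (Introduction). Confidence level 95%, taken as two-sided, z = 1.96 (Primary outcomes). The half-width d is not stated and has to be inferred.

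**Reproducing 73.** For one proportion, n = z²·Se(1 − Se)/d². With Se = 0.95 and d = 0.05: 1.96² × 0.95 × 0.05 / 0.05² = 72.99, so 73.

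The text calls this a power calculation, but one-sample power formulas at 80% power (an assumed value) and alpha 0.05 do not give 73 for contrasts within 90–99%. They give about 183 (one-sided) or 238 (two-sided) for 0.90 against 0.95, 122 or 163 for 0.95 against 0.99, and 41 or 56 for 0.90 against 0.99. So 73 behaves as a precision figure.

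The overall figures use a different half-width. With d = 0.10, n = 18.25 positives; 18.25/0.30 = 60.8, so 61 pairs, and 18.25/0.20 = 91.2, so 92 pairs.

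**Same half-width, other sensitivities (d = 0.05).**

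| Sensitivity | Source | Positives needed | Half-width with 73 |
|---|---|---|---|
| 95% | planning value | 73 | ±5.0 points |
| 91.8% | upper limit, bacterial PCR | 116 | ±6.3 |
| 90% | low end of quoted range | 139 | ±6.9 |
| 86.5% | bacterial PCR estimate | 180 | ±7.8 |
| 79.5% | lower limit, bacterial PCR | 251 | ±9.3 |

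For the 86.5% row: 1.96² × 0.865 × 0.135 / 0.05² = 179.4, so 180; and 1.96 × √(0.865 × 0.135 / 73) = 0.078.

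**Ratio.** (0.865 × 0.135)/(0.95 × 0.05) = 0.1168/0.0475 = 2.46. This ratio is the same for any fixed half-width, so it does not depend on the inferred ±5 points.

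**What 73 bacterial positives would show.** 63 detected of 73 is 86.3%. The Wilson interval is 76.6% to 92.4%; the exact interval is 76.2% to 93.2%.

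**Feasibility.** Even if every positive were bacterial, 179.4 positives imply 179.4/0.30 = 598 pairs at 30% positive, or 179.4/0.25 = 718 at 25%. The section says fewer than 600 samples will suffice. Reaching ±5 points for bacteria is therefore not a realistic demand on this trial; stating the precision it will have is.

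**The case against.** Several points on the other side have weight.

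- *The half-width is inferred.* True. The number 73 also equals total pairs at ±10 points and 25% prevalence (18.25/0.25 = 73.0). But the text says positive samples, and the factor of about 2.5 holds on either reading.
- *The 90–99% may be the interval aimed for around 95%, not a range of planning values.* This is possible and fits the arithmetic. Then 86.5% is not outside a planning range, and the 90% row loses its special status. The figure of 73 is still tied to 95%.
- *The bacterial evidence is mixed.* The Introduction also cites a study of viruses and bacteria in children that found no significant difference in detection for any agent. The reference standard behind 86.5% is not described, and the planning section rests on other sources not shown here. So 86.5% is not established as the true bacterial value; it is the only bacterial PCR sensitivity the protocol puts a number on.
- *The section hedges.* It describes its assumptions as general and open to slight change, speaks of key subgroups, and makes no analysis conditional on reaching 73. Fig 2 is not visible and may plot lower sensitivities. But a 2.5-fold change is not slight.
- *±7.8 points is still tighter than the ±10 behind the overall figures.* Correct: at ±10 points, 86.5% needs only 45 positives. This is why the point calls for a correct statement rather than more patients.

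A reader might go further and infer that a single "reaching a final margin of 0.10 after 500 participants have been recruited" would hide a bacterial shortfall behind good viral results. The documents do not support that. Decision rules and the interim objectives put the comparison on accuracy, not sensitivity. The accuracy deficit is 1 − [prevalence × Se + (1 − prevalence) × Sp]. At Se = 86.5%, with prevalence 20–30% and specificity assumed at 95–100%, it runs from 0.20 × 0.135 = 0.027 to 0.30 × 0.135 + 0.70 × 0.05 = 0.076. It stays below 0.10, so at those prevalences applying the margin by class would not flag the shortfall either. The margin is an interim rule for stopping for inferiority, subject to a committee decision, and is not a criterion for success. Viral and bacterial results are already to be analysed separately, so a shortfall would appear in the estimates, though imprecisely.

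**Conclusion.** The point holds as a misstatement of subgroup precision. The minimum of 73 is right for ±5 points at 95% sensitivity and for no lower value. At the protocol's own bacterial PCR figure, the same precision needs 180 positives (116 to 251 over the cited interval), and 73 give about ±7.8 points.

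This rests on the half-width of 5 points inferred from exact reproduction, on the normal-approximation formula, and on taking 86.5% as a plausible value for rectal swabs against bulk faeces. It does not show that bacterial sensitivity will be that low, that the trial is too small overall, or that the interim rule would conceal a poor bacterial result. The estimates stay valid; what needs correcting is the stated adequacy of 73 for bacterial targets.

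**What to change.** In Sample size calculation:

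1. State the half-width behind 73 (apparently ±5 points at 95% confidence) and describe the figure as one of precision.
2. Say that 73 applies only where sensitivity is about 95%, for example for viral targets.
3. For bacterial targets, add that 73 positives give about ±8 points at 86.5%, and that ±5 points would need about 180.

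In the analysis text, say that the bacterial subgroup result already planned, and any claim that swabs can replace bulk faeces for bacteria, will be interpreted with that wider precision and separately from the viral result.

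The cost is a few sentences. No added recruitment and no new analysis is required. The downside is that the stated precision for bacteria becomes less favourable.
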